#### Secondary outcome measures

Postoperative complications including wound infection, rates of haematoma, seroma, hernia recurrence, intestinal obstruction, intestinal fistula, entocele, mesenteric thrombosis, femoral vein thrombosis, ischaemic orchitis, painful ejaculation, varicocele and scrotal oedema at postoperative 1 week, 1 and 3 months and 1 and 2 years.

#### Other outcome measures.

Quality of life is evaluated by the SF-36.^21^The SF-36 is a 36-item, patient-reported survey of patient health. It consists of eight scaled scores, including vitality, physical functioning, bodily pain, general health perceptions, physical functioning, emotional functioning, social functioning and mental health. The score of each scale is summed and then standardised according to the formula: standardised score = (actual raw score—lowest possible raw score)/possible raw score range×100. The total SF-36 score is the standardised score based on the sum of the eight scaled scores. A higher score indicates better quality of life.

The cost utility analysis of therapeutic regimens involving different surgical approaches will be analysed. Medical costs consist of direct medical and non-medical costs. The direct medical costs include drug charges, inspection fees, laboratory fees, treatment fees, nursing fees and bed charges. The direct medical costs during hospitalisation will be calculated according to the hospital information system. Direct medical costs during the follow-up period will be reported by patients and/or their relatives. Direct non-medical costs include payments for transportation to receive medical care, cost of nutritional supplementation and the costs for accompanying family members during the treatment period.

All outcome evaluations will be independently performed by an experienced assessor blinded to the treatment regimens. The schedule of outcome measurement assessment is shown in table 3.

**Table 3 T3:** Timing of outcome measurement assessment

	Before surgery	During surgery	Follow-up				
	Visit 1 (at admission, day 0)	Visit 2 (at discharge)	Visit 3 (1 week after surgery)	Visit 4 (1 month after surgery)	Visit 5 (3 months after surgery)	Visit 6 (1 year after surgery)	Visit 7 (3 years after surgery)
Signed informed consent	X						
Inclusion/exclusion criteria	X						
Demographic data	X						
Medical insurance type	X						
Delayed visit and admission	X						
Previous history of diseases	X						
Previous history of drug	X						
Risk factors	X						
Disease attack and admission *	X						
Type of hernia (indirect hernia, direct hernia)	X						
Vital sign†	X						
Laboratory examination ‡	X	X					
Imaging examination §	X						
Electrocardiography	X						
Treatment regimen ¶		X					
VAS score **						X	X
SF-36 score			X	X	X	X	X
Medical cost		X	X	X	X	X	X
Concomitant treatment	X	X					
Adverse events Wound infection Haematoma Seroma Hernia recurrence		X	X	X	X	X	X

*Indicates the interval from the first appearance of the lump or main symptoms.

†Indicates body temperature, pulse, respiration rate, and blood pressure.

‡Indicates routine blood testing, coagulation testing, testing of blood glucose, lipids and electrolytes and hepatic and renal function.

§Indicates ultrasound, CT examination.

¶Indicates inguinal hernia-specific treatment.

**Indicates the VAS pain score.

SF-36, 36-Item Short Form Health Survey; VAS, Visual Analogue Scale.

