**Figure 1 F1:**
[figure not shown]
Flow chart of study protocol. VAS, Visual Analogue Scale; SF-36, 36-Item Short Form Health Survey.

Predischarge, and 1 week, 1 and 3 months, 1 and 2 years after surgery: pain, wound infection, haematoma and seroma in the inguinal region and hernia recurrence will be recorded. Medical costs during hospitalisation and patient quality of life after discharge will be also recorded. The flow chart of study protocol is shown in figure 1. And The Standard Protocol Items: Recommendations for Interventional trials (SPIRIT checklist (Standard Protocol Items: Recommendations for Interventional Trials)) was followed in designing the study protocol (see online supplementary file 2).

10.1136/bmjopen-2017-016481.supp2Supplementary file 2

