### Follow-up

Visit 3 (1 week after surgery via clinic visit or telephone follow-up)36-Item Short Form Health Survey (SF-36) score;Medical costs;Hernia recurrence (date and severity of recurrence). Recurrence will be diagnosed by the medical institutions, after being alerted by patients that symptoms are present.Presence or absence of haematoma and/or seroma;Wound infection (date and severity of wound infection).

Visit 4 (1 month after surgery via clinic visit or telephone follow-up)SF-36 score;Medical costs;Hernia recurrence (date and severity of recurrence). Recurrence will be diagnosed by the medical institutions, after being alerted by patients that symptoms are present.Presence or absence of haematoma and/or seroma;Wound infection (date and severity of wound infection).

Visit 5 (3 months after surgery via clinic visit or telephone follow-up)SF-36 score;Medical costs;Hernia recurrence (date and severity of recurrence). Recurrence will be diagnosed by the medical institutions, after being alerted by patients that symptoms are present.Presence or absence of haematoma and/or seroma;Wound infection (date and severity of wound infection).

Visit 6 (1 year after surgery via telephone follow-up)VAS pain score;SF-36 score;Medical costs;Hernia recurrence (date and severity of recurrence). Recurrence will be diagnosed by the medical institutions, after being alerted by patients that symptoms are present;Presence or absence of haematoma and/or seroma;Wound infection (date and severity of wound infection).

Visit 7 (2 years after surgery via telephone follow-up)VAS pain score;SF-36 score;Medical costs;Hernia recurrence (date and severity of recurrence). Recurrence will be diagnosed by the medical institutions, after being alerted by patients that symptoms are present;Presence or absence of haematoma and/or seroma;Wound infection (date and severity of wound infection).

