### Statistical analysis

Statistical analysis will be performed by a statician using SPSS V.19.0 software (SPSS). Continuous variables will be statistically described using the mean, SD, median, minimum and maximum. The categorical variables will be expressed using numbers and percentages.

The analysis will be performed on the basis of the intention-to-treat principle. Descriptive statistics of baseline information will be performed. The χ^2^ test or Fisher's exact test will be used for analysis of categorical variables, such as the incidence of postoperative chronic pain (primary outcome measure) and the incidence of postoperative complications (secondary outcome measure) between groups. Independent sample t-test or Mann-Whitney U test will be used for comparisons of continuous variables, such as SF-36 score, between groups. Cost-utility analysis will be used for economic evaluation, and sensitivity analysis of cost and utility will be performed.

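### SF-36 is first measured 1 week after surgery, so quality-of-life and cost-utility comparisons cannot be adjusted for their own baseline

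*Protocol article*

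**What the plan says.** Under Other outcome measures, "Quality of life is evaluated by the SF-36", and no other quality-of-life instrument is named. Each scale is rescaled to 0–100, and then "The total SF-36 score is the standardised score based on the sum of the eight scaled scores". The scales are given as "vitality, physical functioning, bodily pain, general health perceptions, physical functioning, emotional functioning, social functioning and mental health".

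The same section announces the economic evaluation: "The cost utility analysis of therapeutic regimens involving different surgical approaches will be analysed". Statistical analysis adds: "Cost-utility analysis will be used for economic evaluation, and sensitivity analysis of cost and utility will be performed". No source for the utility is named. That section plans a t-test or Mann-Whitney test for SF-36, with no baseline term.

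On timing, the text beneath Figure 1 says that "patient quality of life after discharge will be also recorded". The first SF-36 entry in the visit lists is under Follow-up: "Visit 3 (1 week after surgery via clinic visit or telephone follow-up)36-Item Short Form Health Survey (SF-36) score". The admission list (visit 1, under Study flowchart) and Table 2 include a VAS pain score but not SF-36. Table 3 marks SF-36 at visits 3 to 7 only.

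Two other places point the other way. The Abstract (Methods and analysis) has primary and secondary outcomes assessed before surgery as well as after. The Discussion (Significance of this study) counts quality of life and cost-utility as secondary outcomes, whereas the outcome section files them under other measures.

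**The concern.** Quality of life and cost-utility are two of the three features that the article says distinguish this trial from related studies. Both appear to rest on SF-36, and its first value is taken after the intervention. A 1-week score may already reflect the operation, so it cannot stand in for a baseline.

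Without a preoperative score, between-patient differences that existed before surgery stay in the error term of every SF-36 comparison. A chance difference between arms at entry can be neither seen nor removed. The same applies to quality-adjusted life-years derived from SF-36. An analysis plan can add a model, an index or a scoring rule later. It cannot supply a questionnaire that was never given, and the number of patients without one grows with each operation.

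**Working it through.** **1. Schedule.** The relevant places, side by side:

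| Place | SF-36 before surgery? |
|---|---|
| Visit 1 list, Study flowchart | No (VAS pain is listed) |
| Table 2, baseline information | No |
| Text beneath Figure 1 | Quality of life after discharge |
| Follow-up | Starts at 1 week |
| Table 3 | Visits 3 to 7 only |
| Abstract, with the Discussion's classification | Implied yes |

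Five places agree that there is none. The contrary reading needs two statements combined: the Abstract's general sentence and the Discussion's labelling of quality of life as secondary. The Abstract's own secondary outcome is complications. The schedule is therefore clear, and the general statements do not match it.

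**2. Plan's own figures.** The document gives no figure for SF-36 precision. Its sample size of 600 is built on chronic pain rates of 10% and 3.4%. It reproduces at 300 per arm (two-sided α 0.05, power 90%, no continuity correction) but has no bearing here. The one checkable count is the scale list: 8 entries, 7 distinct names.

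**3. Precision lost.** Let ρ be the correlation between baseline SF-36 and the outcome compared (a later score, or the quality-adjusted life-year total). The documents do not give ρ, so a range is assumed. With equal variances in the two arms, baseline adjustment multiplies the variance of the treatment difference by 1 − ρ². The sample-size equivalent is 1/(1 − ρ²).

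| Assumed ρ | 1 − ρ² | Variance reduction | Equivalent sample-size ratio |
|---|---|---|---|
| 0.4 | 0.84 | 16% | 1.19 |
| 0.5 | 0.75 | 25% | 1.33 |
| 0.6 | 0.64 | 36% | 1.56 |

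**4. Chance imbalance.** Suppose the arms differ by 0.01 in utility at entry. This is an assumption. For scale, with 300 per arm and an assumed utility SD of 0.10 to 0.15, one standard error of the baseline difference is SD × √(2/300), or 0.008 to 0.012. If the fraction ρ of the imbalance persists (equal variances over time), the shift in a 2-year total is ρ × 0.01 × 2 = 0.008, 0.010 and 0.012 for ρ = 0.4, 0.5 and 0.6. The ceiling, if all of it persisted, is 0.01 × 2 = 0.02.

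**5. Area under the curve.** Take measurement times of 0, 1, 4.33, 13, 52 and 104 weeks. The trapezoid weight of the day-0 point is (1/2)/104 = 0.0048, about 0.5% of the 2-year area. The missing baseline therefore barely affects the area itself. Its value lies in adjustment. (The 2-year horizon follows the Follow-up section. Table 3 heads the last visit as 3 years, and the two need reconciling.)

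**The case against.** The strongest case against runs as follows. This is a condensed article, and the choice of utility index and the calculation of quality-adjusted life-years are commonly left to a fuller protocol or analysis plan. Allocation is randomised within centre, so unadjusted comparisons from 1 week onward are unbiased. Other baseline variables, VAS pain among them, could serve as covariates. The day-0 point carries about 0.5% of the area. The outcome section does not rank these measures as primary or secondary, and the primary outcome and sample size are untouched.

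Most of that stands, and it rules out three stronger readings that a reader might infer:

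- *The cost-utility analysis has no utility, or would yield cost per SF-36 point.* The documents do not say that the 0–100 total is the utility. The 36 items are collected, and a preference-based index can be derived from them.
- *The score double-weights physical functioning, or SF-36 is reduced to one total.* A repeated name in a descriptive list is most likely a wording slip, and no scoring rule shows double-weighting. The scale scores are standardised in their own right, with the total in addition.
- *Quality-adjusted life-years cannot be formed.* Unadjusted ones can. Only adjustment for their own baseline is blocked, and only by the missing measurement.

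A repeated-measures model in place of the planned tests would be a preference, not a correction. What the objection does not answer is the schedule itself. It is stated consistently, conflicts with the Abstract and Discussion read together, and cannot be repaired at analysis. Other covariates may recover part of the precision, but not adjustment for the outcome's own starting value.

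**Conclusion.** The point holds as one about precision and robustness, not bias or invalidity. No SF-36 is scheduled before surgery, so neither SF-36 comparisons nor quality-adjusted life-years derived from SF-36 can be adjusted for their own baseline. The forgone gain is a variance reduction of about 16% to 36% for correlations between 0.4 and 0.6. These correlations are assumed, and the trial states no precision target for SF-36 against which to set them. The imbalance figures rest on an assumed entry difference of 0.01, only part of which would be expected to persist.

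Two wording matters are minor: the described 0–100 total is not a preference-based utility, and the list of eight scales contains seven distinct names. The chronic-pain analysis is unaffected. The change is worth making because it is cheap and because the loss becomes permanent for each patient operated on without a baseline.

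**What to change.** 1. Add SF-36 to visit 1 in the Study flowchart list, Table 2 and the pre-surgery column of Table 3. Bring the text beneath Figure 1 into line. Use one classification of quality of life and cost-utility in the outcome section and the Discussion.
2. Adjust the SF-36 and quality-adjusted life-year comparisons for baseline score and centre.
3. Keep patients already enrolled without a baseline in the analysis, using a standard missing-baseline method such as mean imputation of the baseline covariate.
4. State that utility comes from a preference-based index derived from the SF-36 items (SF-6D, for example).
5. Correct the scale list to eight distinct scales.

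The cost is one questionnaire at an existing admission visit, plus wording. The downside is that recruitment began in February 2017 and was ongoing at submission, so an unknown share of patients will have no baseline. The gain shrinks accordingly: if a fraction f has a baseline and the rest are mean-imputed, the variance reduction is roughly f × ρ². With f = 0.5 and ρ = 0.5, both purely illustrative, that is 0.5 × 0.25 = 12.5% instead of 25%. Recruitment was expected to run to December 2019, so the earlier the amendment, the more of the gain is kept.

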### AE and serious AE

According to the study protocol and clinical judgement, AE/serious AE (SAE) occurring after herniorrhaphy will be reported to the Department of General Surgery, the Fourth Affiliated Hospital of China Medical University.

AE refer to any adverse medical events occurring after herniorrhaphy in patients or clinical subjects. SAE refer to any adverse postoperative medical events involving one or more of the following criteria:Death, irrespective of the cause;Life-threatening event;Severe or permanent disability or organ dysfunction;Haemorrhage;Malformation, birth defect;Hospitalisation or extended hospital stay;Readmission to hospital;Recurrence (symptomatic) of inguinal hernia.

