Bahram^15^	RCT	TAPP (n=150) Lichtenstein (n=150)	Inguinal herniajrnlTblFoot	Three hundred patients with inguinal hernia were enrolled in this study, divided into two equal groups: Group I managed by TAPP laparoscopic repair and group II managed by open lichtenstein repair.	Operative time, intraoperative visceral injury, ileus, hospital stay or wound complications, postoperative pain, groin hypothaesia, return to activities, recurrence	TAPP technique is an excellent approach for treatment of inguinal hernia in comparison to LR either unilateral or bilateral, primary or recurrent inguinal hernia with low morbidity and recurrence comparable to that oflichtenstein repair with advantages of less postoperative pain and early return to activities.

LR, laparoscopic repair; RCT, randomised controlled trial; TAPP, transabdominal preperitoneal; VAS, Visual Analogue Scale.

There are few reports on the effects of different inguinal hernia repair approaches on postoperative complications, particularly regarding severe postoperative complications, in patients in northern China. The incidence of severe complications after inguinal hernia repair is relatively low, but this surgery can lead to physical impairment or organ dysfunction that greatly decreases patient quality of life and places a heavy burden on the patient’s family and society. At present, there is a scarcity of clinical evidence from large sample, randomised controlled trials investigating the effectiveness of inguinal hernia repair via the anterior transversalis fascia approach versus the preperitoneal approach.

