### Methods/Design

#### Study design

This is a prospective, large-sample, multicentre, randomised controlled trial that will include a cohort of over 720 patients with inguinal hernia. The trial committee organisation and contributions and role are provided in the see online supplementary file 1. In strict accordance with the Consolidated Standards of Reporting Trials standards,^16^ the baseline data (preoperative data), therapeutic regimen, therapeutic outcome and medical costs during hospitalisation of patients with inguinal hernia will be recorded. Patient data will be collected using an electronic data capture system (EDC).

10.1136/bmjopen-2017-016481.supp1Supplementary file 1

According to recommendations for treatment and follow-up of inguinal hernia repair in adults in the Guidelines for the Diagnosis and Treatment of Inguinal Hernia in Adults (2014 Edition) formulated by Chinese scholars^17^ and the Adult Inguinal Hernia Treatment Guidelines (Updated Edition in 2014) developed by the European Hernia Society,^18^ patients who undergo herniorrhaphy will be followed up at seven time-points: at baseline (at admission, visit 1), predischarge and at 1 week (visit 2), 1 month (visit 3), 3 months (visit 4, clinic visit or telephone follow-up), 1 year (visit 5, telephone follow-up) and 2 years after surgery (visit 6, telephone follow-up). The flow chart of the study protocol is shown in figure 1. Prior to surgery: patients will be rescreened against inclusion and exclusion criteria. Signed informed consent will be obtained. Patient’s demographic data, history of disease and medication and admission condition and vital signs will be recorded. Clinical examination data will be collected from each centre, including history of disease, physical examination, laboratory testing results, imaging findings, preoperative VAS pain score, intraoperative findings and details of occurrence and management methods of intraoperative injury to the intestinal tract and bladder, spermatic cord and vascular system.

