### AE reporting

Reporting time limit for AE will be within 24 hours of onset. In the clinical research period (from the time of signing informed consent to 1–2 years postoperatively), any AE occurring in any patient who received either surgical approach will be properly treated. According to the requirements of this study protocol and clinical evaluation, researchers will fill in the table of Adverse Events After Herniorrhaphy and submit this within 24 hours to the Clinical Research Center of Abdominal Wall Hernia, the Fourth Affiliated Hospital of China Medical University, China.

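### Adverse events are defined as starting after the operation but their reporting period starts at consent, so the intraoperative injuries that centres record have no settled place as adverse events or stated outcomes

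*Protocol article*

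**What the plan says.** Five parts of the protocol article bear on this.

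- **AE and serious AE.** "AE refer to any adverse medical events occurring after herniorrhaphy in patients or clinical subjects". For serious events: "SAE refer to any adverse postoperative medical events involving one or more of the following criteria". The criteria that follow include haemorrhage, organ dysfunction and a longer hospital stay.
- **AE reporting.** The period runs "from the time of signing informed consent to 1–2 years postoperatively", with a report due within 24 hours. The form to be completed is nevertheless titled as covering events after herniorrhaphy.
- **Study design.** Each centre is to collect "intraoperative findings and details of occurrence and management methods of intraoperative injury to the intestinal tract and bladder, spermatic cord and vascular system".
- **Secondary outcome measures.** "Postoperative complications including wound infection, rates of haematoma, seroma, hernia recurrence, intestinal obstruction, intestinal fistula", followed by further postoperative conditions such as ischaemic orchitis and femoral vein thrombosis. No intraoperative injury is on the list.
- **Main objectives and Statistical analysis.** Both speak of postoperative complications. The chi-square or Fisher test is given for categorical variables, with chronic pain and postoperative complications as the examples.

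**The concern.** The trial compares two surgical approaches, and some of the harm from an operation occurs during it. The investigators evidently consider injury to bowel, bladder, cord and vessels worth recording, since centres must document both its occurrence and its management. The definition of an adverse event then begins after the operation, the complication outcome is postoperative, and the reporting period begins before the operation.

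Two things are at stake. First, an organ or vessel injury that is recognised and repaired on the table may count in no stated safety measure, which weakens a comparison meant to weigh the advantages and disadvantages of each approach. Secondly, safety counts depend on consistent reporting. If one centre follows the definition and another follows the reporting period, the same injury is an AE in one and not in the other. Randomisation is stratified by centre, so a difference in practice between centres would fall on both arms. Surgeons are not blinded, however, so case-by-case discretion over what to report could differ by arm.

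**Working it through.** The plan gives no figure on this point, so there is none to reproduce. The check sets the sections side by side and follows two cases through them.

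**Case A: an injury made and repaired at surgery, with no later consequence.**
- Study design: recorded, both occurrence and management.
- AE and serious AE: not an AE, because it did not occur after the operation. Not an SAE, because it was not postoperative.
- AE reporting: it falls inside the period, which opens at consent. The section relies on the term AE, though, and its form is titled as post-herniorrhaphy, so the section does not itself settle whether the injury is reportable.
- Secondary outcome measures: not listed.
- Statistical analysis: not named.

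**Case B: an injury at surgery followed by, for example, an intestinal fistula or a longer stay.**
- The fistula is a listed secondary outcome, and the longer stay meets an SAE criterion. The consequence is counted.
- The injury itself is still named in no outcome.

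The gap is therefore Case A. In Case B the harm reaches the comparison through its consequence.

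**Table 3.** The adverse-event row is marked from Visit 2, whose column is headed as during surgery but sub-headed as at discharge. The Predischarge section also places Visit 2 before discharge. The items named in the row are wound infection, haematoma, seroma and recurrence. The table neither clearly captures intraoperative events nor clearly excludes them.

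**Scale, by assumption only.** The documents give no rate of intraoperative injury. The number expected among all randomised patients is 720 × rate:
- 0.2%: 720 × 0.002 = 1.4
- 0.5%: 720 × 0.005 = 3.6
- 1%: 720 × 0.01 = 7.2
- 2%: 720 × 0.02 = 14.4

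These rates are illustrative and have no source in the documents. They count all injuries, so the Case A number is at most this large at each rate. The finding does not depend on them.

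**The case against.** A reader might infer that the trial leaves intraoperative injuries out of every safety and complication comparison. The documents do not support that.

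- No section excludes them. The list of variables to be tested is illustrative, and the Interim analysis section refers to a separate statistical analysis plan. Neither that plan nor the full protocol is at hand, and either may tabulate the recorded operative findings.
- Nor is it established that such injuries escape the 24-hour report. That holds only if the definition overrides the reporting period, and nothing says which governs.
- Important injuries are partly captured through their consequences: fistula, obstruction, ischaemic orchitis, femoral vein thrombosis, haemorrhage, organ dysfunction, longer stay.
- The objective is itself limited to postoperative complications, so objective, secondary outcome and planned test agree with one another. Naming intraoperative injury widens the scope; it does not repair a mismatch between objective and outcome.
- Precedent in the article is thin. In Table 1, one of the five listed trials has it among its outcomes ("Operative time, intraoperative visceral injury, ileus, hospital stay or wound complications"); the other four do not.

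All of this stands against the stronger reading. It leaves the narrower point intact. What counts as an AE is a protocol definition, stated here, and it conflicts with the period stated under AE reporting. An analysis plan can tabulate the injuries, but it cannot make centres report them consistently as adverse events.

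**Conclusion.** The point holds as an internal contradiction together with a gap in the stated outcomes. The AE and SAE definitions begin after surgery, the AE period begins at consent, and injuries that centres must record are named in no stated outcome or comparison. Read literally, the definition leaves an injury repaired at surgery without a listed consequence outside AE, SAE and the secondary outcome.

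The number of affected events is unknown, because the documents give no rate. They also do not show that visceral or vascular injury is where the two approaches differ most. The article describes different access routes and goes no further. The conclusion rests on the article's wording alone and assumes that the documents not shown do not already reconcile the two sections. It is a modest correction, worth making because it removes a contradiction and uses data already to be collected.

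**What to change.** 1. In AE and serious AE, reword both definitions to agree with the consent-onward period in AE reporting, so that intraoperative events count as AE and, where a criterion is met, as SAE. Retitle the reporting form to match.
2. In Secondary outcome measures, add intraoperative injury to bowel, bladder, spermatic cord and vessels as a secondary safety outcome, compared by randomised arm with the tests already planned for categorical variables. Show it beside the postoperative complications so that the latter remain readable on their own.
3. In Table 3, state at which visit the injury record is entered, and check that the eCRF (not shown) holds it in analysable form.

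The cost is small: wording, possibly one eCRF item, and a few more AE/SAE reports. Recruitment is under way, so the new outcome for patients already operated on should come from the existing injury records. The added outcome should go through the ethics approval described under Protocol modification.
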